## 6. Parkinson's Disease Rating Scale

### 6.1. Statistical Analysis

All data will be analyzed using intention-to-treat (ITT) analysis and the per-protocol set (PPS) for coherence. As in stage one, normality tests will be performed on the measurement data. A *t*-test will be performed for variables found to be normally distributed, and the rank-sum test will be used for those not normally distributed. The rank-sum test and nonparametric test will be used for the graded data, and the chi-square test will be applied to counted data. Repeated-measurements ANOVA will be used for the UPDRS, Hoehn–Yahr, HAMA, and SF-36 scales. The rank-sum test will be used to compare efficacy.

### 6.2. Ethical Issues in Stages 1 and 2

The trial will be conducted according to the guidelines of the Declaration of Helsinki.

The study was approved by the Ethics Committee of the First Affiliated Hospital of Guangzhou University of Traditional Chinese Medicine (No. K [2021] 021). All the participants will be asked to provide informed consent before participating in the trial.

### 6.3. Quality Control in Stages 1 and 2

A research workbook will be established. All the investigators will be trained and tested for conformance with preset standards before the beginning of each stage. Each participant will have a fixed physician and time points for treatment to ensure consistency in the intervention effect. Since the use of anti-Parkinson drugs will affect the physician's evaluation of patient symptoms, the participants will be evaluated for PD symptoms 4 hours after taking their medication.

All acupuncturists participating in this project have received formal education at Traditional Chinese Medicine universities, obtained physician qualification certificates, and possess more than 3 years of clinical experience in acupuncture.

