## 5. Statistical Analysis

To ensure the integrity and accuracy of data, two statisticians will independently perform statistical analyses using Statistics 26.0 (IBM SPSS Statistics Inc., Chicago, USA), establish the database, and provide proofreading for logic. Enumeration data will be expressed as percentages, whereas measurement data will be expressed as mean ± standard deviation. A normality test will be performed for the measurement data. For variables that are determined to be regularly distributed, a *t*-test will be employed, and for those that are not, a rank-sum test will be utilized. The rank-sum test and nonparametric test will be employed for graded data, and the chi-square test will be applied to counted data. Repeated-measures analysis of covariance (ANCOVA) will be used for the UPDRS, Hoehn–Yahr, HAMA, and SF-36 scales. The rank-sum test will be applied to compare efficacy. Serological index values will be analyzed using covariance. Two-sided tests will be used for all hypothesis testing, with *P* < 0.05 as the standard of statistical significance.

Stage Two: if the efficacy of acupuncture with anti-Parkinson drugs for PDA is found to be better than that of the sham acupuncture, excluding the possible placebo effect of acupuncture, stage 2 will be conducted to assess the compliance, viability, universality, and cost effectiveness of acupuncture for PDA.  Figure 6 depicts a flowchart of the second step.Diagnostic criteria:  The diagnostic criteria for stage 2 are the same as those for stage 1Participant inclusion criteria:  The inclusion criteria for stage 2 are the same as those for stage 1Participant exclusion criteria:  The exclusion criteria for stage 2 are the same as those for stage 1

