#### 5.2.3. Outcome Measurements

HAMA score will be the primary outcome. The primary outcomes will be measured at baseline and week 4. Moreover, universality, feasibility, cost effectiveness, Hoehn–Yahr Rating Scale score, UPDRS score, and serological indicators will be considered the secondary outcomes. Hoehn–Yahr Rating Scale score, UPDRS score, and serological indicators will be measured at baseline and week 4. Universality, feasibility, and cost effectiveness will be measured at week 4. In addition, the universality and feasibility study will employ questionnaires administered by the physicians, and cost effectiveness will be calculated as the ratio of HAMA score improvement to treatment cost. Furthermore, side effects will be assessed during the trial. The timeline of the outcome measurements is shown in Table 2.

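### Stage 2 omits the covariance analysis that stage 1 names for the serum markers, leaving them by its own text to a t-test or rank-sum rule with no baseline covariate

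*Protocol article*

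**What the plan says.** **Stage 1 (section 5, Statistical Analysis).** The general rule for measurement data starts with a normality test: "For variables that are determined to be regularly distributed, a *t*-test will be employed", with a rank-sum test otherwise. Two groups of outcomes then get their own method. For the scales: "Repeated-measures analysis of covariance (ANCOVA) will be used for the UPDRS, Hoehn–Yahr, HAMA, and SF-36 scales". For the serum markers: "Serological index values will be analyzed using covariance". The covariate is not named.

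**Stage 2 (section 6.1, Statistical Analysis).** The section opens with "As in stage one, normality tests will be performed on the measurement data" and repeats the general rule: a t-test under normality, and "the rank-sum test will be used for those not normally distributed". The scales again get their own method: "Repeated-measurements ANOVA will be used for the UPDRS, Hoehn–Yahr, HAMA, and SF-36 scales". There is no sentence on the serum markers.

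**Stage 2 measurements (section 5.2.3).** The serum markers are secondary outcomes, and the sampling times are fixed: "Hoehn–Yahr Rating Scale score, UPDRS score, and serological indicators will be measured at baseline and week 4". Table 2 agrees.

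**The concern.** The same four markers (CRF, ACTH, CORT and 5-HT) are secondary outcomes in both stages, and both stages take a sample at baseline and at week 4. Stage 1 names a covariance analysis for them. The stage 2 section follows the stage 1 list closely, drops that one item and gives no reason. An analyst working from section 6.1 would find only the t-test/rank-sum rule to apply to a continuous serum level.

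What is at stake is precision. With two time points and a randomised comparison, ANCOVA with baseline as covariate has a lower variance than a test on week 4 values whenever the two time points are correlated. It also has a lower variance than a test on change from baseline whenever that correlation is below 1. Stage 2 collects everything that this analysis needs.

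**Working it through.** **1. Which stage 2 rule reaches the markers?**

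| Item | Section 5 (stage 1) | Section 6.1 (stage 2) |
|---|---|---|
| Normality test | yes | yes, tied to stage 1 |
| t-test or rank-sum for measurement data | yes | yes |
| Rank-sum/nonparametric for graded data | yes | yes |
| Chi-square for counts | yes | yes |
| UPDRS, Hoehn–Yahr, HAMA, SF-36 | repeated-measures ANCOVA | repeated-measures ANOVA |
| Rank-sum to compare efficacy | yes | yes |
| Serum markers | covariance | no entry |

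The reference back to stage 1 in section 6.1 is attached to the normality tests only, so it does not bring the covariance sentence with it. The markers are neither graded data nor counts, and they are not in the repeated-measures list. The t-test/rank-sum rule is the only one left.

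**2. Inputs for the size.**
- n = 37 evaluable per arm, two-sided 5%, 80% power, 1:1 allocation (sections 5.1 and 5.1.1). This sample size was set for HAMA; no figure is stated for the markers.
- The marker effect is an assumption: the standardised difference d that gives a week 4 t-test 80% power at 37 per arm.
- ρ, the baseline to week 4 correlation of a marker, is an assumption: 0.3 to 0.7.

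**3. The assumed effect.** By the normal approximation, d = (1.960 + 0.842) × √(2/37) = 0.651. By the noncentral t, d = 0.660. The power figures below agree under both to the digits shown.

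**4. Variance relative to a week 4 test.**
- Week 4 values only: 1
- Change from baseline: 2(1 − ρ)
- ANCOVA on baseline: 1 − ρ²
- ANCOVA over change score: (1 − ρ²) / [2(1 − ρ)] = (1 + ρ)/2, below 1 for any ρ < 1

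**5. Power.** The effective standardised difference is d divided by the square root of the variance factor. Worked case, ρ = 0.5, ANCOVA: 0.660/√0.75 = 0.762, which at 37 per arm gives 89.9%.

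| ρ | Week 4 t-test | Change-score t-test (variance factor) | ANCOVA (variance factor) | Variance cut by ANCOVA against week 4 test |
|---|---|---|---|---|
| 0.3 | 80% | 65.8% (1.40) | 83.6% (0.91) | 9% |
| 0.5 | 80% | 80.0% (1.00) | 89.9% (0.75) | 25% |
| 0.6 | 80% | 87.9% (0.80) | 93.8% (0.64) | 36% |
| 0.7 | 80% | 95.1% (0.60) | 97.5% (0.51) | 49% |

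ANCOVA has the highest power in every row. Its advantage over the better of the other two tests is about 4 points at ρ = 0.3, 10 at 0.5, 6 at 0.6 and 2 at 0.7.

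**The case against.** The strongest objection is that section 6.1 never assigns the markers to a t-test or rank-sum test. The assignment is reached by elimination in a condensed article, and a full analysis plan may name a model. The general rule also stands in section 5 beside the covariance sentence, so the rule alone does not exclude covariance. This limits the weight of the point but does not remove it. The article does not stay silent on marker analysis: it names a method for stage 1 and prints a parallel list for stage 2 without it. As printed, the two sections disagree.

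Two stronger readings are tempting, and the documents support neither.

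- *Stage 2 throws away its baseline sample.* Section 6.1 does not say whether the tests use week 4 values or changes from baseline. A test on changes would use the baseline sample, only less efficiently than ANCOVA.
- *The two stages' marker results cannot be compared.* No cross-stage comparison of markers is planned, and the controls differ in any case: sham acupuncture in stage 1, and anti-Parkinson drugs with clinical monitoring only in stage 2. Under randomisation, a t-test and a baseline-adjusted ANCOVA target the same mean difference; only the rank-sum branch would change the measure.

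It is also fair to say that section 5 names no covariate. Baseline is the natural reading, but it is a reading. Finally, the gain may be small: about 2 points over a change-score test at ρ = 0.7, and under 4 points over a week 4 test at ρ = 0.3.

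**Conclusion.** The point holds as an inconsistency between sections 5 and 6.1 with a modest cost in precision. Allocation is randomised, so the missing covariate does not bias the stage 2 comparison, and the primary HAMA result is untouched.

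The size is illustrative. It rests on an assumed marker effect, an assumed correlation of 0.3 to 0.7, and the 37 per arm planned for HAMA. Within that range, baseline-adjusted ANCOVA gives about 84% to 97.5% power. The corresponding figures are 80% for a week 4 t-test and about 66% to 95% for a change-score t-test. Because section 6.1 leaves week 4 values or changes open, the actual loss could lie against either comparator. This is a desirable improvement to a secondary analysis, not a defect that threatens the trial's conclusions.

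**What to change.** In section 6.1, add a sentence: week 4 CRF, ACTH, CORT and 5-HT are each compared between arms by ANCOVA with the baseline value of the same marker as covariate, on the log scale where a marker is skewed. In section 5, name the baseline value of the marker as the covariate in the existing serology sentence, so that the two sections agree.

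The log scale and the named covariate go beyond what section 5 now says. They are added so that skewness can be handled without falling back on an unadjusted rank-sum test, and so that the model is fixed in both stages.

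The cost is one new sentence and one clarified sentence. Sampling, visits and patient numbers stay as they are.

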### 5.1. Sample Size

The sample size was calculated using the primary outcome, which is the shift in HAMA score from baseline. According to preliminary results, the mean HAMA score in patients who received acupuncture combined with anti-Parkinson drugs was 15.8, while it was 13.9 in patients who received anti-Parkinson drugs alone. According to PASS 15.0, a sample size comprising 74 patients (37 in each group) would have a power of 80% or more to identify a two-sided significance level of 5%. The overall sample size needed for the study is 82 (41 in each group), anticipating a 10% dropout rate. If a patient cannot adhere to a course of acupuncture, patient's condition suddenly worsens during the treatment process, and the treatment plan of anti-Parkinson drugs needs to be changed, the treatment will be stopped.

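### Stage 2 assigns HAMA, measured only at baseline and week 4, to repeated-measures ANOVA; a baseline-adjusted ANCOVA would use the same data more efficiently and remove doubt about which result tests treatment

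*Protocol article*

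**What the plan says.** Section 5.2.3 makes HAMA the stage 2 primary outcome and fixes its timing: "The primary outcomes will be measured at baseline and week 4". Table 2 agrees, with HAMA marked at weeks 0 and 4 only.

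Section 6.1 gives the method: "Repeated-measurements ANOVA will be used for the UPDRS, Hoehn–Yahr, HAMA, and SF-36 scales". It names no baseline covariate and does not say which term of the ANOVA tests treatment. The same section lists a t-test or rank-sum test chosen after a normality test, rank methods for graded data, and a rank-sum test for comparing efficacy. It states both an intention-to-treat and a per-protocol analysis.

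Section 5.1 sizes the stage on change: "The sample size was calculated using the primary outcome, which is the shift in HAMA score from baseline". The planning means are given as "the mean HAMA score in patients who received acupuncture combined with anti-Parkinson drugs was 15.8" and "while it was 13.9 in patients who received anti-Parkinson drugs alone", with 37 per group for 80% power at two-sided 5%. No SD is stated.

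For stage 1, section 5 says "Repeated-measures analysis of covariance (ANCOVA) will be used for the UPDRS, Hoehn–Yahr, HAMA, and SF-36 scales", again without naming the covariate.

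**The concern.** A repeated-measures ANOVA on two values must take baseline as one of its levels. It then offers two between-group results, and neither makes good use of the baseline. The main effect mixes a pre-randomisation value, where the expected difference is zero, with the week-4 value. The interaction subtracts the whole baseline from week 4 instead of adjusting for it by regression, and so carries more noise than it needs to.

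At stake are some precision on the primary outcome and a clear statement of which result answers the question. The second is made worse by the t-test and rank-sum routes in the same section, which leave several candidate tests for HAMA. A smaller inconsistency is that Hoehn–Yahr, an ordinal stage, goes through ANOVA although the section sends graded data to rank methods.

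**Working it through.** **Inputs from the article (section 5.1):** difference 15.8 − 13.9 = 1.9; 37 per arm; 80% power; two-sided 5%; 1:1 allocation.

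**Assumed, because not stated:** the SD, the correlation r between baseline and week-4 HAMA (range 0.3 to 0.7), and equal variances at the two visits.

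**Step 1: the plan's own figure.** Without an SD, 37 per arm cannot be reproduced independently, only solved backwards.
- Normal formula: SD = 1.9 / [(1.960 + 0.842) × √(2/37)] = 2.92.
- Noncentral t: SD = 2.88, so d = 1.9/2.88 = 0.66.

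This SD can be read in two ways. Section 5.1 sizes on the shift from baseline, which points to the SD of change. It also labels the two means as HAMA scores, which leaves the SD of the week-4 score possible. Both are carried through.

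**Step 2: what each analysis estimates.** Let Δ be the treatment difference and σ the SD of a single score.

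| Analysis | Expected estimate | SD per patient |
|---|---|---|
| ANOVA, group main effect | Δ/2 | σ√((1+r)/2) |
| ANOVA, group-by-time interaction (change score) | Δ | σ√(2(1−r)) |
| ANCOVA, week 4 on group and baseline | Δ | σ√(1−r²) |

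The variance ratio of ANCOVA to change score is (1−r²)/(2(1−r)) = (1+r)/2, which is 0.65, 0.75 and 0.85 at r = 0.3, 0.5 and 0.7.

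**Step 3: numbers at r = 0.5, where the two readings coincide (σ = 2.88).** The standard error is the SD × √(2/37), that is, SD × 0.2325.
- Main effect: estimate 0.95, SD 2.49, SE 0.58, power 36.6%.
- Interaction: estimate 1.9, SD 2.88, SE 0.67, power 80.0%.
- ANCOVA: estimate 1.9, SD 2.49, SE 0.58, power 89.9%.

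In 20,000 simulated trials the mean estimate was 0.957 for the main effect and 1.90 for the interaction. Simulated power was 37.1% (main effect), 80.0% (interaction) and 89.7% (ANCOVA, with its 71 residual degrees of freedom).

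**Step 4: range of r, 37 per arm (noncentral t).**

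| Reading of 2.88 | r | Main effect | Interaction | ANCOVA |
|---|---|---|---|---|
| SD of change | 0.3 | 53.8% | 80% | 93.5% |
| | 0.5 | 36.6% | 80% | 89.9% |
| | 0.7 | 21.7% | 80% | 86.0% |
| SD of week-4 score | 0.3 | 41.2% | 65.8% | 83.6% |
| | 0.5 | 36.6% | 80.0% | 89.9% |
| | 0.7 | 33.0% | 95.1% | 97.5% |

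On the first reading, ANCOVA would reach 80% power with about 24, 28 and 31 per arm (normal formula).

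**Step 5: unequal variances.** The entry window (HAMA 14 to 29) may make the baseline variance smaller than the week-4 variance. With slope b and residual variance s², the ANCOVA variance is s² and the change-score variance is s² + (1−b)² × Var(baseline). Illustration with assumed values: SDs of 1 and r = 0.6 give b = 0.6, s² = 0.64 and a ratio of 0.64/0.80 = 0.80. Halving the baseline SD gives 0.64/(0.64 + 0.16 × 0.25) = 0.64/0.68 = 0.94. The advantage of ANCOVA shrinks, so the figures in step 4 may overstate it.

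**The case against.** The strongest defence is that the interaction tests exactly the outcome on which the stage was sized, the shift in HAMA from baseline, and is unbiased for it. On the natural reading of the back-solved SD, it also keeps the planned 80% power at every r. Which ANOVA term is reported is detail that an analysis plan can settle. ANCOVA is then a more efficient choice, not the repair of an invalid one. This stands, and it limits the point to efficiency and clarity.

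Several stronger readings are tempting and are not supported:
- A reader might infer that the plan will halve the treatment effect. Nothing in the article makes the group main effect the treatment test; halving follows only if that line is read as the answer.
- A reader might infer that the stage falls short of its planned power. That holds only if 2.88 is the week-4 SD and r is below 0.5, and the article states neither.
- A reader might infer that the 14 to 29 entry window is where change scores do worst, because it lowers r. Step 5 shows the opposite: a smaller baseline variance brings the change score closer to ANCOVA.
- A reader might infer that stage 1's model should simply be carried over. Stage 1 has two post-baseline HAMA visits (weeks 4 and 12) and an unnamed covariate, so its repeated-measures model does not transfer to a single post-baseline value.

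The defence does not answer the efficiency argument itself. Under 1:1 randomisation ANCOVA is never asymptotically less precise than the change score, and the baseline is already measured.

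**Conclusion.** The point holds as one of efficiency and clarity. The interaction in the stage 2 ANOVA is valid but leaves baseline information unused. The main effect would estimate 0.95 where the difference is 1.9 and should be ruled out as the treatment test. Baseline-adjusted ANCOVA is at least as precise in all but trivial cases, where the single degree of freedom outweighs the gain.

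The direction does not depend on the unstated SD or r; the size does. For r from 0.3 to 0.7 with equal variances, ANCOVA adds about 14 down to 6 percentage points of power if the implied SD is that of change (93.5 − 80; 86.0 − 80). It adds about 18 down to 2 if the SD is that of the week-4 score (83.6 − 65.8; 97.5 − 95.1). The gain is smaller if the baseline variance is below the week-4 variance.

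**What to change.** In section 6.1:
1. Name one primary HAMA analysis for stage 2: ANCOVA of week-4 HAMA on treatment group and baseline HAMA, in all randomised participants, reporting the adjusted difference with its 95% confidence interval.
2. Use the same form for UPDRS and SF-36.
3. State that the t-test and rank-sum routes, including the rank-sum comparison of efficacy, are not the primary HAMA test.
4. Analyse Hoehn–Yahr as ordinal, in line with the section's own rule for graded data.

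The cost is a few sentences of wording and one degree of freedom. Baseline HAMA is already collected, so no visits, measurements or patients are added, and the stated sample size need not change.

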## 7. Discussion

Anxiety is more common in PD patients than in the general population [20]. PDA may be related to L-DOPA treatment, dopamine deficiency etiology, and complex PD symptoms.

The symptoms of PD are complex. In addition to motor symptoms, there are a series of nonmotor symptoms, such as sleep disorder, constipation, and depression. These complex symptoms seriously affect the quality of life of patients, resulting in emotional burden and provoking the development of disorders such as anxiety. Deficiency of dopamine in PD results in increased firing rate of the locus coeruleus (LC), which suppresses the synthesis and release of the 5-HT neurons and thereby aggravates the anxiety levels in patients with PD. However, excessive dopamine intake can easily affect the balance between dopamine and 5-HT, resulting in PDA. The decrease of endogenous dopamine in the striatum of PD patients and the excessive intake of dopamine during long-term drug use easily cause the occurrence of PDA. PDA may be an adverse outcome of disease progression in PD.  Figure 7 shows the possible pathogenesis of PDA and the relationship between PD and PDA [21, 22]. Relevant studies proved that acupuncture can supplement dopamine by maintaining the stability of dopamine in the substantia nigra striatum so as to avoid hyperactivity or lack of dopamine [23].

At present, anxiety is often neglected as one of the nonmotor symptoms of PD, and there is no drug for the treatment of PDA; hence, antianxiety drugs and antidepressant drugs are mainly used. However, antidepressant drugs, such as serotonin reuptake inhibitors (SSRI), combined with anti-Parkinson drugs, such as monoamine oxidase B inhibitors (MAO-BI), can easily aggravate tremor symptoms [24]. There is a lack of clinical evidence regarding the role of antianxiety drugs in PDA; only anecdotal evidence exists. Patients with anxiety benefit from more effective and safer forms of complementary and alternative interventions, such as acupuncture [25]. Several related studies have confirmed that acupuncture can improve the nonmotor symptoms of PD [9, 16]. Acupuncture for patients with PDA has not been intensively investigated. We will also investigate the mechanism of action of acupuncture on PDA in terms of the HPA, which is the center of the stress response, and 5-HT in stage 1. CRH, ACTH, and CORT are interrelated and interact within the HPA. When the human body is stimulated by anxiety, CRH can enter the anterior pituitary in the blood of the portal system and stimulate it to release ACTH, resulting in an increase in CORT secretion [26]. Le et al. [27] demonstrated that electric acupuncture was associated with a reduction in depressive symptoms via adjustment of HPA function [27]. Previous animal experiments have confirmed that acupuncture is effective in regulating the levels of HPA-related hormones [28, 29]. Therefore, in stage 1, we aim to explore whether acupuncture improves PDA by regulating the HPA via changes in the CRH, CORT, ACTH, and 5-HT levels.

To reduce bias, we will use a rigorous allocation method with blinded patients, evaluators, and statistical analysts. We will also use a new type of sham acupuncture tool to avoid the placebo effect. Therefore, this trial will potentially provide valid clinical evidence. However, this study has certain limitations. First, owing to the nature of acupuncture, the operator cannot be blinded in this study. However, we will ensure the blinding of the participants, evaluators, and statistical analysts. Second, although we strictly require no increase or decrease of the medication dosage of the participants during treatment, it is difficult to monitor the self-medication of patients. Third, although a strict sample size calculation was carried out for this study, the participants will be recruited from only one hospital, which may lead to a lack of representativeness of the data.

Whether a treatment measure is suitable for clinical application and promotion needs to be comprehensively considered from the aspects of clinical efficacy, cost and economic benefits, patient acceptance, and feasibility. Therefore, this study has two stages. Stage 1 of this study hypothesizes that patients with PDA receiving acupuncture will have a reduction in anxiety as a result of adjustments to the HPA on the basis of excluding the placebo effect. Stage 2 of this study hypothesizes that acupuncture to relieve PDA has the characteristics of high feasibility, fewer side effects, high patient compliance, and reasonable cost effectiveness. It will not add additional economic burden to patients and their families while providing a curative effect and improving the quality of life of patients. It is a treatment method with clinical promotion and application value. The second stage is a supplement to the first stage. We designed this two-stage trial to observe whether acupuncture has clinical application value in the treatment of PDA.

The findings of this study will help to validate the effects and mechanism of acupuncture as a complementary treatment method for PDA. The study has the potential to provide strong clinical evidence as well as new guidelines for the treatment of PDA.

